### Secondary aims

The secondary aims will be to describe baseline factors associated to exercise tolerance improvement following exercise training or early training interruption.

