### Randomisation

The participants will be randomised in variable blocks by centres. Enrolled patients will be randomised to either an intervention or a control group (randomisation ratio 1:1). The allocator will be a researcher not involved in the study, blinded on group allocation. The allocator will generate a randomisation list by a dedicated software (https://www.randomizer.org/). When a new patient (after control of eligibility and signing of informed consent) will need to be enrolled, care providers from each centre will contact the randomisation centre by phone for definitive allocation. Patients will be aware of their allocation.

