### Statistical analysis

#### Sample size

We propose a sample size based on an effect size of treatment of 130 s of difference in seconds of CWRET between the groups. The estimated improvement (mean and standard deviation) in the control group was calculated in relation to previous studies [36], defining 150 s as the minimally clinically important difference of improvement of CWRET after rehabilitation. The improvement in the treatment group was estimated by an internal pilot study conducted in 10 patients. A total of 156 participants would provide 90% power to detect 130 s (SD 250) difference between the groups, with 5% significance. Due to a high expected drop-out rate (patients transferred to acute care, severely ill with fever, severe dyspnoea, acute respiratory failure, etc.) we will enrol at least 170 patients. We expect a recruitment rate of at least 23 patients per centre.

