#### Analysis plan

Details about project start-up phase and patient recruitment are reported in ClinicalTrials.gov ID NET03322787. Statistical analysis will be performed using STATA 11 (StataCorp LLC, Texas 77845–4512 USA).

Continuous variables with normal distribution will be presented as mean ± standard deviation (SD), if non-normally distributed, as median and interquartile range. The distribution of continuous variables will be verified by the Shapiro–Wilk test. Binary and categorical outcomes will be described using frequencies and percentages in each group.

The primary analysis will be a modified intention-to-treat analysis, including all randomly assigned participants for whom data on the primary endpoint is available. Secondary analysis will be conducted per-protocol (all completers).

Primary analysis of the primary outcome will be through a linear regression model considering the outcome measures at the end of the training as a dependent variable and intervention/control as an explanatory variable with adjustment for the baseline value of the primary outcome. The model will also take into account the centre as a stratification variable.

The baseline, follow-up values and the unadjusted change in outcome measures between baseline and the end of study for both groups will be also presented.

Secondary analysis will consist of a two-sample *t* test comparing differences in the changes in all outcome measures after rehabilitation between the intervention and control groups.

In order to define which baseline characteristics are related to the improvement of primary outcome and to drop-out event, we will perform an explanatory data evaluation analysing the odds ratio (with corresponding 95% confidence intervals and *P* values) of improvement/non-improvement on CWRET above 150 s [36] and the completion/dropout of the programme for each baseline variable. A *P* value of < 0.05 will be considered statistically significant.

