## Discussion

Aerobic exercise training in severe and very severe COPD with chronic respiratory failure has been not well studied [6, 7] despite high workload, unbearable exercise-induced dyspnoea [9] and frequent premature interruption of exercise creating a significant limitation to exercise for these patients. Non-pharmacological strategies such as NIV have been proposed [5] to reduce this discomfort, with inconclusive and variable results due to poor tolerance and the high expertise and time-consumption required from health professionals during exercise sessions [13]. Theoretically, HFNT could obtain similar results (in terms of exercise tolerance) with less discomfort and time required.

The use of the HFNT device will not change the underlying disease process, but we expected that (at least for a subgroup of patients) its use during moderate or high intensity training will further improve functional capacity, exercise tolerance, respiratory and peripheral muscle strength, blood gases, disability, symptoms, impact of disease and quality of life, with high patient satisfaction. Future studies may investigate the applicability and benefits of the routine application of this device in severe COPD and CRF.

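### The predictor analysis splits CWRET change at 150 s and applies P<0.05 to every baseline variable: it loses power, invites chance findings and leaves the odds ratio for baseline CWRET hard to interpret

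*Protocol article*

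**What the plan says.** The Secondary aims section sets out to "describe baseline factors associated to exercise tolerance improvement following exercise training or early training interruption". The Analysis plan section serves that aim with an evaluation that it calls explanatory: odds ratios, 95% confidence intervals and P values for "improvement/non-improvement on CWRET above 150 s [36] and the completion/dropout of the programme for each baseline variable". The same section ends with one rule, not limited to any analysis, that a P "value of < 0.05 will be considered statistically significant".

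The Sample size section takes 150 s from a cited source as the minimally important improvement in CWRET after rehabilitation. The primary analysis, also in the Analysis plan section, is different in kind: a linear regression of end-of-training CWRET on arm, adjusted for baseline CWRET and taking centre into account.

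**The concern.** The protocol fixes the outcome, the effect measure, the scope and the decision rule for this analysis, so the method itself can be judged. Three features are weak.

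- A measured time is cut into two classes, although the same section already models it as continuous for the primary outcome.
- Every baseline variable is examined against two binary outcomes under an unqualified 5% rule.
- CWRET at T0 is one of those baseline variables and is also subtracted to form the change being predicted.

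At stake is what the trial reports on its secondary aim. Real predictors may be missed, chance ones may be called significant, and an association between low (or high) baseline endurance and improvement may be read as clinical when it partly reflects how the change score is built.

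**Working it through.** **Plan's own figure.** The Sample size section gives an "effect size of treatment of 130 s of difference in seconds of CWRET between the groups" and states: "A total of 156 participants would provide 90% power to detect 130 s (SD 250) difference between the groups, with 5% significance". With "randomisation ratio 1:1" and a two-sided test, n per arm = 2 × (1.960 + 1.282)² × (250/130)² = 2 × 10.51 × 3.698 = 77.7, so 78 per arm and 156 in total. The figure reproduces. Below, 250 s is taken as the SD of change within an arm.

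**Number of tests.** The protocol gives no list, so the count is read from the Outcome measures sections.
- Recorded at T0 only: age, sex, BMI, FEV1, FVC, FEV1/FVC, comorbidity scale = 7. Diagnosis is not counted, since all patients have COPD.
- Outcome measures also taken at T0: CWRET, 6MWT, MIP, MEP, biceps, quadriceps, MRC, PO2, PCO2, PO2/FiO2, pH, Barthel Index, Barthel Dyspnoea Index, CAT, MRF-26 = 15.
- Total 22 variables × 2 outcomes = 44 tests.

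If all nulls are true, the expected number of false positives is 22 × 0.05 = 1.1 per outcome and 44 × 0.05 = 2.2 overall. If the tests were also independent, the chance of at least one would be 1 − 0.95^22 = 0.68 per outcome and 1 − 0.95^44 = 0.90 overall.

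**Information kept by the split.** For a normal outcome cut so that a share p respond, relative efficiency = φ(c)²/[p(1 − p)], where c is the normal quantile of the cut. If the mean change is 150 s in controls and 150 + 130 = 280 s with HFNT, the responder shares are 50% and 70%. If the means are 20 s and 150 s, they are 30% and 50%.
- p = 0.5: 0.3989²/0.25 = 0.64.
- p = 0.3 or 0.7: 0.3477²/0.21 = 0.58.

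Simulated power at N = 156, with arms 130 s apart and a 5% test (2,000 trials per setting):

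| Correlation of predictor with change | Change kept continuous | Split at 150 s |
|---|---|---|
| 0.20 | about 0.69 | about 0.49 |
| 0.25 | about 0.87 | about 0.67 |
| 0.30 | about 0.96 | about 0.83 |

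**Baseline CWRET against its own change.** With ρ the T0–T1 correlation and k = SD at T1 / SD at T0, corr(T0, change) = (ρk − 1)/√(1 + k² − 2ρk). The protocol gives neither ρ nor k, so both are assumed over a range (N = 156, SD of change 250, split at 150 s, 1,500 trials per row):

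| k | ρ | corr(T0, change) | T0 CWRET at P<0.05 |
|---|---|---|---|
| 1 | 0.5 | −0.50 | 99.9% |
| 1 | 0.7 | −0.39 | 97% |
| 1 | 0.8 | −0.32 | 86% |
| 1.25 | 0.7 | −0.14 | 26% |
| 1.25 | 0.8 | 0.00 | 4.7% |
| 1.5 | 0.7 | +0.05 | 7.4% |
| 2 | 0.8 | +0.45 | 99.4% |

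If measurement error is the only link (assumed T0 SD 100–250 s, reliability 0.70–0.95), T0 CWRET is significant in about 5% to 84% of simulated trials.

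**Drop-outs.** The protocol says "we will enrol at least 170 patients". If exactly 170 enrol and 156 complete, 170 − 156 = 14 drop out (8.2%). For a continuous factor, the difference detectable with 80% power is then (1.96 + 0.84) × √(1/14 + 1/156) = 0.78 SD, an odds ratio of about e^0.78 = 2.2 per SD.

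**The case against.** The best defence is that the aim is secondary and descriptive. Confidence intervals are already planned, and 150 s is a cited clinical threshold fixed in advance. The primary analysis keeps CWRET continuous. Much of this stands. Strict family-wise control is not obligatory here, and the threshold justifies reporting a responder result. It does not justify making the split the only analysis of the aim, and a general P<0.05 sentence turns description into significance testing.

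Some stronger readings are tempting but not supported:

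- A reader might infer that a spurious effect of baseline CWRET is certain. It is not: at k = 1.25 and ρ = 0.8 the correlation is zero, and at larger k it turns positive.
- A reader might infer that 6MWT and muscle strength inherit the same distortion. Nothing in the protocol allows this to be calculated. The CWRET load is set from each patient's own T0 6MWT, so a strong link between walking distance and CWRET time cannot be presumed.
- A reader might infer that the arms are pooled without a treatment term. The article is silent on covariates here, and such detail may sit in a fuller document.
- A reader might fault the analysis for not showing who benefits from the device, since the Discussion expects benefit "at least for a subgroup of patients". The stated aim is prognostic. That phrase is a passing expectation and not a planned analysis.
- The 90% chance of at least one false positive assumes independent tests. Several variables are plainly correlated (FEV1, FVC and their ratio; PO2 and PO2/FiO2), which lowers that chance but not the expected count of 2.2.

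**Conclusion.** The concern holds as a weakness of method in the secondary predictor analysis. The loss of information is firm: about 36–42% for responder shares between 30% and 70%, assuming roughly normal change. The expected 2.2 false positives rest on a count of 22 variables and on all nulls being true; fewer variables would reduce it in proportion. For baseline CWRET the mechanism is certain, but its size and direction are not. Simulated significance runs from about 5% to nearly 100% over the assumed inputs, so an odds ratio for this variable could not be read as a predictor effect whichever way it fell. The figure of 14 drop-outs is a difference between two planned totals, not a forecast. The protocol says at least 170 and expects high drop-out, so the number may be larger.

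None of this touches the primary analysis or the sample size. It is worth changing because a better model already stands in the same section.

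**What to change.** In the Analysis plan section:

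- For improvement, regress continuous T1 CWRET on each baseline factor, with T0 CWRET, arm and centre in the model. Once T0 is in the model, a factor's coefficient is the same for T1 as for change, so coupling no longer enters it. Do not interpret T0 CWRET as a predictor of its own change.
- Keep the odds ratio for improvement above 150 s as a supportive result.
- Label the predictor and drop-out analyses exploratory. Report estimates with 95% CIs, and state that the P<0.05 rule does not apply to them.
- With about 14 drop-outs, describe the drop-out odds ratios only and say that they are imprecise.

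The cost is analysis wording, with no new data or patients. The downside is that no significant-predictor claims can be made. The power figures above compare continuous with split change; the gain under the T1 model was not simulated separately and will depend on how strongly a factor is correlated with T0 CWRET.

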### Data sharing

Individual participant data that will underlie the results to be reported in the results article, after deidentification (text, tables, figures and appendices) will be available for meta-analysis after article publication. Those interested will be able to request the data from the corresponding author by mail.

### Dissemination of findings

Authorship on peer-reviewed manuscripts will be offered to those who have made a significant contribution to the conception or design of the project or the acquisition, analysis, or interpretation of data for the work, and/or drafted the work or reviewed it critically for important intellectual content. There are no publication restrictions for this research. Dissemination of results will be via traditional channels of journal publications and scientific conferences.

## Discussion

Aerobic exercise training in severe and very severe COPD with chronic respiratory failure has been not well studied [6, 7] despite high workload, unbearable exercise-induced dyspnoea [9] and frequent premature interruption of exercise creating a significant limitation to exercise for these patients. Non-pharmacological strategies such as NIV have been proposed [5] to reduce this discomfort, with inconclusive and variable results due to poor tolerance and the high expertise and time-consumption required from health professionals during exercise sessions [13]. Theoretically, HFNT could obtain similar results (in terms of exercise tolerance) with less discomfort and time required.

The use of the HFNT device will not change the underlying disease process, but we expected that (at least for a subgroup of patients) its use during moderate or high intensity training will further improve functional capacity, exercise tolerance, respiratory and peripheral muscle strength, blood gases, disability, symptoms, impact of disease and quality of life, with high patient satisfaction. Future studies may investigate the applicability and benefits of the routine application of this device in severe COPD and CRF.

## Data Availability

During the time course of the study, the database will be closely related to the principal investigator and managed by the data manager. All data generated or analysed during this study will be included in the subsequently published results article (and its supplementary information files).

## Abbreviations

6MWT: 6-min Walking Test
COPD: chronic obstructive pulmonary disease
CRF: chronic respiratory failure
CWRET: Constant Work Rate Exercise Test
FEV1: forced expiratory volume in 1 s
FiO_2_: inspiratory fraction of oxygen
FVC: forced vital capacity
HFNT: high-flow nasal therapy
NIV: non-invasive ventilation
SpO_2_: blood oxygen saturation
T0: baseline
V-mask: Venturi-mask
WOB: work of breathing
